# Effectiveness of intravaginal electrical stimulation combined with electromyography biofeedback-mediated pelvic floor muscle training for postpartum symptomatic pelvic organ prolapse: protocol for the PROSPECT randomized trial

**DOI:** 10.1186/s13063-022-06051-z

**Published:** 2022-02-09

**Keywords:** Prolapse, Pelvic floor muscle, Biofeedback, Electrical stimulation, Quality of life, Economic evaluation

## Abstract

**Background:**

Pelvic organ prolapse (POP) is seen in up to 30–70% of women presenting for routine gynecology care and 10% of women suffering from bothersome POP symptoms. Vaginal childbirth is one of the most prominent contributing factors for POP. Pelvic muscle training (PFMT) is considered effective to improve mild to moderate POP symptoms. In addition, higher-intensity, supervised PFMT aided by biofeedback and electrical stimulation may confer greater benefit. However, the long-term efficacy of the PFMT combined with electromyography biofeedback is unknown, which indicates the need for further evidence.

**Methods:**

This multicenter randomized controlled trial compares the effectiveness and cost-effectiveness of conventional PFMT versus biofeedback-mediated PFMT plus neuromuscular electrical stimulation (NMES) for postpartum symptomatic POP women. The primary outcome is the proportion of patients with the improvement of at least one POP-Q stage at 36 months after randomization. The primary economic outcome measure is incremental cost per quality-adjusted life year at 36 months. Two hundred seventy-four women from four outpatient medical centers are randomized and followed up with pelvic floor examination, questionnaires, and pelvic ultrasonography imaging. All participants are arranged for three appointments over 12 weeks. NMES and electromyography biofeedback via intravaginal probe are added to PFMT for participants in the biofeedback-mediated PFMT group. Group allocation could not be blinded from participants and healthcare staff that deliver intervention but remain masked from medical staff that carry out PFM assessment. An intention-to-treat analysis of the primary outcome will estimate the difference of the proportion of POP-Q stage improvement between the trial groups right after the intervention, and during the follow-up until 36 months, using the chi-square test and multilevel mixed models respectively. A logistic regression analysis was used for adjusting for important baseline variables that are unbalanced.

**Discussion:**

The trial results will provide evidence of the effectiveness of electromyography biofeedback-mediated PFMT in improving women’s POP-Q staging, quality of life, and cost-effectiveness.

**Trial registration:**

CCTR Registry ChiCTR210002171917. Registered on March 6, 2019

## Background and rationale {6a}

Pelvic organ prolapse (POP), encompassed in the spectrum of pelvic floor dysfunction (PFD), is a common condition characterized by a descent of the female pelvic organs (bladder, uterus, and rectum) from the normal anatomic position into or through the vagina [1]. Half parous women have varying degrees of POP, and one in 12 women suffered from bothersome POP symptoms [2] which negatively influence women’s social, physical, and psychological well-being [3]. Direct medical cost for PFDs is estimated to total $412 million for ambulatory care and $1012 million for POP surgery annually in the USA [4]. The number of patients in need of POP treatment is on a rapid rise due to an aging population and an improving awareness [5]. Treatment for POP includes conservative options (like pelvic floor muscle training, PFMT) and surgery. The former is recommended for all POP patients and particularly helpful for those with a mild to moderate degree of prolapse [6–8], while the latter is reserved for those having severe symptomatic prolapse with the goal of anatomical restoration and symptom relief [1]. Given the substantial societal and economic burden, there is a growing demand to identify and validate more tailored and effective treatment strategies addressing the pathogenesis of POP.

POP’s most consistent risk factors include vaginal delivery, previous hysterectomy, menopausal state, high body mass index, and genetic background [5], all of which result in weakened pelvic floor musculature and connective constructure. With direct damage to the fetal passage, vaginal delivery is one of the most prominent contributing factors to POP. Delancey et al. [9] reported that childbirth-induced injury of levator ani presented in 55% of women with prolapse, yet only 16% in those with normal support. Reportedly 56% primiparous and 58.8% multiparous women manifest different levels of PFM strength impairment early postpartum [10, 11], paralleled with the time POP commonly develops. The incidence rate of stage 2–4 prolapse (determined by the Pelvic Organ Prolapse Quantification System, POP-Q) during this period is estimated as high as 64% among primiparous women [12]. Early postpartum intervention has been reported to ameliorate PFM morphology and function. Patients that initiated PFMT 6 weeks after delivery demonstrated increased PFM strength and endurance. Further stratum of those with a major defect of levator ani muscle showed 45% less chance of having vaginal symptoms in the PFMT group [13–15]. However, a systemic review [16] identified little benefit of postnatal PFMT in treating urinary and fecal incontinence more than 3 months postpartum, presumably attributed to a spontaneous discontinuation of PFMT and an increasing burden on the pelvic floor which resulted from holding the growing newborn. Follow-up data beyond the first postpartum year is extremely rare. High-quality evidence evaluating postnatal PFMT remains a necessity.

PFMT improves strength, endurance, coordination, and timing of PFM contraction; facilitates appropriate muscle tone during relaxation; and hypertrophies the pelvic floor, thereby aiding in structural support [17–20]. However, when executing a conventional PFMT, more than 30% of women are unaware what muscles they have actually recruited when voluntarily training themselves, and also what muscles they are supposed to activate and how for an effective contraction [21, 22], which partially account for the mixed results of the efficacy of PFMT in individual studies. That is where neuromuscular electrical stimulation (NMES) and electromyography biofeedback kick in as an adjunct. NMES stimulates PFM activity in a similar way our nerve system does, except that lack of motivation and fatigue may jeopardize our adherence to voluntarily, sufficiently, and continually exercising our PFM, whereas an NMES program automatically turns PFMT into a supervised routine [23]. Meanwhile, signals from our nervous system may not pick up enough fibers, as nerves and neuromuscular junctions are stretched, compressed, and frequently impaired along pregnancy progression and when babies push through [24], while external signals from the NMES device might hopefully be capable of. Electrical impulses generated by an NMES device are delivered through electrodes bedded on an intravaginal probe or under a skin pad to targeted nerves and muscle fibers to elicit PFM contraction [21, 25]. Within EMG biofeedback, EMG delineating the superposition of electrical potentials arising from activated muscle fibers is collected via electrodes and processed into visual and auditory guidance, leading patients to a correct contraction. Targeted signals enable selective training and thus strengthening of individual muscles [26]. Visualization of contraction and responsive instruction add more interaction to basic PFMT, potentially promoting practice initiative and body awareness.

Despite that NMES has been trialed and reviewed for years in verification of its theoretical advantages [27–29], few studies have featured the real-world effect of NMES and biofeedback combined PFMT on postpartum POP, and they generally assessed treatment response symptom-wise. Therefore, we will supplement our trial with more objective measurements, including the morphology and electrophysiology of PFM, the anatomical staging of POP, and the cost analysis. In combination, they are intended to test our hypothesis that NMES combined PFMT may have a superior efficacy on POP with better modulation of intrinsic PFM. This approach excels for it digs deeper to the root of POP.

### Objectives {7}

In this study, we aim to determine whether PFMT assisted by NMES and EMG biofeedback, in comparison to conventional PFMT, brings forth more satisfactory short-term and long-term changes anatomically and clinically among early postpartum POP patients and to compare the cost-effectiveness of both training programs.

## Methods

### Trial design {8}

PROSPECT (to treat *pro*lapse *s*uffered *p*ostpartum with *e*lectrical stimulation-*c*ombined *t*raining of pelvic floor muscle) study comprises a two-armed, multicenter randomized controlled trial (Fig. 1). We anticipate to recruit 274 eligible primiparas in the 6th postpartum weeks and randomly assign them (by sealed envelope) on a 1:1 ratio into an experimental group that receives NMES and EMG biofeedback-mediated PFMT and a control group that receives conventional PFMT alone. Group allocation could not be blinded from participants. Within a 3-year follow-up, we will continuously monitor the effect on POP by measuring:
Commonly mentioned POP-related symptoms with questionnairesAnatomic position of pelvic organs and morphology of pelvic floor through POP-Q staging and ultrasonographyPFM strength by digital palpation under the Modified Oxford ScalePFM electromyography employing the Glazer Protocol

**Fig. 1 Fig1:**
[figure not shown]
Flow chart of PROSPECT study

The cost-effectiveness of NMES and EMG biofeedback combined PFMT will be established by comparing direct medical costs (costs for outpatient consultations, treatment devices usage, absorbent pads, and surgery when required) from hospital documentation and participant-completed questionnaires.

### Methods: participants, interventions, and outcomes

#### Study setting {9}

The RCT will simultaneously take place in 4 centers spanning northeast and southwest China, namely Beijing Hospital, Beijing Friendship Hospital, Beijing Dongcheng District Health and Family Planning Service Center, and First People’s Hospital of Yunnan Province. All of them are academic hospitals equipped with NMES devices and well-trained staff specializing in pelvic floor rehabilitation. Registration information will be available on http://www.chictr.org.cn, the official website of Chinese Clinical Trial Registry, a non-profitable organization that has gained membership in WHO ICTRP. An internal pilot initiated in Beijing Hospital is intended to help us accumulate experience and optimize our design for this RCT.

#### Eligibility criteria {10}

##### Inclusion and exclusion criteria for participants

Women meet the inclusion criteria if they are primiparas between 20 and 40 years of age, at the 6th to 8th week after delivering a singleton baby vaginally full-term and non-instrumented, without a vaginal laceration over grade 3, with anatomical evidence of mild to moderate prolapse (2 ≤ POP-Q stage ≤ 3). We excluded women with factors that may confound the evaluation of impacts on pelvic floor function, such as a chronic cough or constipation, POP or UI history prior to pregnancy, previous pelvic surgery, or induced abortion in the mid-trimester. Non-Mandarin speakers and those under conditions like mental disorders or illiteracy are also excluded, as their decision-making and instruction-grasping abilities are impaired. Also considered unqualified for this study are those with contraindications for NMES, including a pelvic malignancy, a genitourinary infection, or an implanted pacemaker.

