#### Recruitment {15}

A postnatal consultation is normally scheduled at the 6th week after delivery in China, during which gestation and childbirth history, POP-Q staging, and digital palpation are routinely taken. All prolapse, structural defects, painful areas on palpation, POP-related symptoms, and functional assessments of PFM are documented. Upon screening of those clinical records, primiparas aged 20–40 with stage 2–3 (in POP-Q system) prolapse who have had full-term non-instrumented vaginal delivery are identified as potential participants for this study. They are referred to a recruitment advertisement with detailed information on study layout and eligibility. If showing interest, they will be given a pamphlet and several days to adequately understand the research. Later on, we will approach them by phone and invite them to a research center in an appointment that is termed the baseline visit.

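### The title and abstract name symptomatic prolapse, but entry requires only POP-Q stage 2–3, so the planned results apply to anatomical prolapse

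*Protocol article*

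**What the plan says.** The Protocol article describes its population in two ways.

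- **Title:** training "for postpartum symptomatic pelvic organ prolapse".
- **Abstract, Methods:** the comparison is made "for postpartum symptomatic POP women".
- **Objectives {7}:** changes are to be studied "among early postpartum POP patients", without the word symptomatic.
- **Eligibility criteria {10}:** primiparas of 20 to 40 years, 6 to 8 weeks after a vaginal delivery, "with anatomical evidence of mild to moderate prolapse", given as POP-Q stage 2 to 3. No symptom is required.
- **Recruitment {15}:** at the routine postnatal visit "POP-related symptoms, and functional assessments of PFM are documented", but the selection rule that follows is "primiparas aged 20–40 with stage 2–3 (in POP-Q system) prolapse who have had full-term non-instrumented vaginal delivery are identified as potential participants".

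The primary outcome is improvement by at least one POP-Q stage. The secondary outcomes include the prevalence of each symptom and mean changes in questionnaire scores, without restriction to women with symptoms at baseline. The primary economic outcome in the abstract is cost per QALY at 36 months. The subgroups listed in {20b} are age and additional moderate-intensity exercise.

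**The concern.** A woman with stage 2 prolapse and no symptoms satisfies {10} and {15}, yet she is outside the population named in the title and abstract. If the trial is run as written and reported under its title, an average over all enrolled women would be credited to symptomatic women, a group that was not selected and for which no separate analysis is listed.

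This matters most for the symptom scores, quality of life and cost per QALY. There, benefit may depend on having symptoms at the start, and readers will take the title as the description of who was treated.

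**Working it through.** **1. Do the selection rules contain a symptom criterion?**

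| Section | Prolapse requirement | Symptom requirement |
|---|---|---|
| Title | prolapse | yes (symptomatic) |
| Abstract, Methods | prolapse | yes (symptomatic) |
| Objectives {7} | prolapse | none stated |
| Eligibility {10} | POP-Q stage 2–3 | none |
| Recruitment {15} | POP-Q stage 2–3 | none; symptoms recorded only |

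The two sections that decide who enters agree with each other and disagree with the title and abstract.

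**2. Does the article treat stage and symptoms as interchangeable?** No. Its background says "Half parous women have varying degrees of POP, and one in 12 women suffered from bothersome POP symptoms". The abstract sets 30–70% with prolapse against 10% with bothersome symptoms. These figures show that one does not imply the other. They do not give the symptomatic share in this trial.

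**3. Is the sample size affected?** Inputs from Sample size {14}: 50% against 20% improved, margin 15 percentage points, one-sided 0.05, 80% power, 20% attrition. With unpooled variance:

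n per arm = [p1(1−p1) + p2(1−p2)] × (z0.95 + z0.80)² / (p1 − p2 − margin)²
= (0.25 + 0.16) × (1.645 + 0.842)² / 0.15² = 112.66, rounded up to 113.

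Attrition: 113 / 0.8 = 141.25, rounded up to 142 per arm, or 284 in total. This reproduces the figure in {14}. (The article gives 274 elsewhere, which is a separate matter.) Symptoms enter nowhere, so 284 changes only if the assumed POP-Q response rates change.

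**4. What could happen to symptom outcomes?** This step illustrates a mechanism and does not estimate anything for this trial. Suppose a share s is symptomatic, only those women can benefit, and the SD is unchanged. The mean effect is then s times the effect in symptomatic women, and the n required grows by about 1/s². Assume a standardised effect of 0.5 in symptomatic women, two-sided 0.05, and 142 × 0.8 ≈ 114 evaluable per arm. Power is about Φ(0.5s × √(114/2) − 1.96):

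| s (assumed) | Mean effect | Power | n per arm for 80% power |
|---|---|---|---|
| 1.0 | 0.50 | 96.5% | 63 |
| 0.8 | 0.40 | 85.5% | 99 |
| 0.6 | 0.30 | 62.0% | 175 |
| 0.4 | 0.20 | 32.6% | 393 |
| 0.2 | 0.10 | 11.4% | 1570 |

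On the same model, with incremental cost unchanged, the QALY gain is multiplied by s and the cost per QALY by 1/s (2 at s = 0.5). Both s and the effect of 0.5 are assumptions; the article gives neither.

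**The case against.** The strongest reply is that this is a matter of labelling. The primary outcome is anatomical, its calculation needs no symptom input, and the mean over all randomised women is a valid estimate for the women enrolled. Symptoms are measured at baseline and follow-up, so a symptomatic subset can be described. The article also refers to a Statistical Analysis Plan and a Health Economic Analysis Plan, which are not shown and may already contain such an analysis. All of this stands, and it limits the point. What remains is that the title and abstract contradict two concordant statements of the entry rule, and no analysis plan can change who was selected.

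A reader might infer more than the documents support:

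- **That symptomatic women will be a small minority.** Dividing the background figures gives (1/12)/(1/2) = 17%, and those in the abstract 10/70 = 14% to 10/30 = 33%, or about 40 to 95 of 284 women. The numerators and denominators come from different groups of women, mix ages and cover all degrees of prolapse. The trial takes primiparas with stage 2–3 at 6 to 8 weeks, so the ratio is no estimate for it and the true share may be much higher.
- **That the symptom and cost-utility results are biased.** They would be averages over a broader group. The error would be to attribute them to symptomatic women.
- **That women without prolapse symptoms have nothing to gain.** PFDI-20 also covers urinary and colorectal-anal symptoms, the Discussion describes prolapse as accompanied by other pelvic floor disorders, and symptoms may appear during 36 months of follow-up. The model in step 4 leaves this out.
- **That the trial cannot inform on symptomatic women at all.** With baseline symptoms recorded, it can, though less precisely.
- **That the 75 women already enrolled entered on the anatomical criterion alone.** Trial status gives the number, not the criterion applied.

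**Conclusion.** The contradiction holds on the face of the article. Under {10} and {15} women without symptoms are eligible, so the results as planned apply to anatomical POP-Q stage 2–3 prolapse and not specifically to symptomatic prolapse.

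The validity of the primary outcome and the 284 are untouched. Average effects on symptom scores and QALYs may be smaller than in symptomatic women if women without symptoms enrol and have less room to improve. The direction rests on that assumption, and the size cannot be estimated from the documents. The point is worth correcting before results are seen because it governs the population to which the conclusions are attached.

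**What to change.** - **Reconcile the population.** Either replace *symptomatic* with *anatomical (POP-Q stage 2–3)* in the title, the abstract and the reported conclusions, or, if symptomatic women were intended, state that criterion in {10} and carry it into {15}. The sponsor must say which was meant.
- **Report the share symptomatic at baseline**, by arm.
- **Add baseline symptom status to the subgroups in {20b}**, with an interaction test for symptom scores and QALYs. Several symptoms and questionnaires are collected but no single symptomatic status is defined, so a definition from these data has to be fixed in advance.
- **Keep the all-randomised analysis as the main one.** Making a separate baseline-symptom subset primary for each symptom would be a debatable preference and is not needed here.

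The cost is a more modest population claim and one further subgroup of limited precision. With equal SD in both groups, the standard error of the interaction is 1/√(s(1−s)) times that of the overall contrast: 1/√0.25 = 2 times at an even split, and more at any other. The anatomical wording needs no new data and no change to 284. A symptom criterion in {10} would narrow the pool of eligible women, and the response rates assumed in {14} would have to be confirmed for that group.

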##### Eligibility criteria for healthcare providers

Therapists involved in this study are experienced and certificated in pelvic floor rehabilitation, all acquainted with the manipulation of relevant devices. They will receive additional training prior to the start of the study. A manual with standard operation protocol (SOP) will be provided to each center covering details on the execution of all procedures adopted in this study. The same equipment and SOP will be employed across centers for standardization.

#### Recruitment {15}

A postnatal consultation is normally scheduled at the 6th week after delivery in China, during which gestation and childbirth history, POP-Q staging, and digital palpation are routinely taken. All prolapse, structural defects, painful areas on palpation, POP-related symptoms, and functional assessments of PFM are documented. Upon screening of those clinical records, primiparas aged 20–40 with stage 2–3 (in POP-Q system) prolapse who have had full-term non-instrumented vaginal delivery are identified as potential participants for this study. They are referred to a recruitment advertisement with detailed information on study layout and eligibility. If showing interest, they will be given a pamphlet and several days to adequately understand the research. Later on, we will approach them by phone and invite them to a research center in an appointment that is termed the baseline visit.

#### Who will take informed consent? {26a}

A principal investigator is designated in each research center to implement the informed consent process throughout the entire time scope of the study. After confirming the inclusion eligibility of potential participants in the baseline visit (see the above section), the investigator will present to them the panorama of this study again, with an emphasis on putative benefits and risks of each intervention and scheduled follow-up visits as well as examinations to be performed during them. The investigator needs to make sure they have thoroughly weighed their decision and that they understand the voluntary nature of their participation where dropout at any point is permitted without punishment. They are notified on the confidentiality of their identity information and the privacy of data management. Written consent is asked if they readily wish to enroll after being fully informed. No study procedures are allowed until the consent has been taken. Participants are entitled to remain informed with the latest updates as the study proceeds.

#### Additional consent provisions for collection and use of participant data and biological specimens {26b}

Not applicable. Consent for the collection and use of participant data is limited to this study.

